It is reported that combined approach is more effective than a single intervention in improving the successful rate of smoking cessation. Therefore, this trial will use a double-blind and double-dummy randomized controlled trial, to explore the efficacy and safety of acupuncture and/or nicotine patch with placebo on smoking cessation, so as to enrich and optimize smoking cessation programs and provide effective smoking cessation methods with lower relapse rates for smokers.

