### Sample size calculation

We will use the calculation formula of sample size of enumeration data in a completely random design, as describe previously. The PASS software will be used for calculation. The formula is listed as follow:$$N=\frac{\Big[{Z}_{\alpha}\sqrt{2p\left(1-p\right)}+{Z}_{\beta }{\sqrt{p_1\left(1-{p}_1\right)+{p}_2\left(1-{p}_2\right)\Big]}}^2}{{\left({p}_1-{p}_2\right)}^2}$$

*α* = 0.05 will be set up as the level of test, and the test power is 90%. The withdrawal rates of acupuncture (*p*_1_) and placebo (*p*_2_) will be 56% [18] and 9.1% [19], respectively; *p* is the mean of *p*_1_ and *p*_2_. The PASS 26.0 software will be used to calculate that the sample size required for each group for ≥18 cases. Considering 30% loss to follow-up rate, the sample size per group will be 24 cases. Consequently, the total number of the participants will be 96, based on 24 case per group in the four groups.

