### Outcomes

#### Primary outcome

Abstinence rate, relapse rate, and expiratory CO value will be selected as the main outcome indexes. The former two are mainly judged by the self-report of the participants at the end of treatment and follow-up, while the expiratory CO content is mainly detected by the CO detector.

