#### Secondary outcome

Secondary measures included a modified Fagerstrom test for nicotine dependence (FTND) score, a Minnesota Nicotine Withdrawal Scale (MNWS), and modified Brief Questionnaire of Smoking Urge (QSU-Brief) score. The three scores will be used to reflect the severity of nicotine dependence, withdrawal symptoms, and smoking craving of the participants. The higher scores indicate, the more severe symptoms. Each patient will be asked a questionnaire prior to the treatment and at 1, 4, and 8 weeks after the treatment. Table 3 shows the specific observation points of each index during the study.

**Table 3 Tab3:** The measurement time points of various indicators

Indicators	Before start of treatment	Treatment period			End of the follow-up
		Week 1	Week 4	Week 8	
Abstinence rate				√	√
Relapse rate					√
Expiratory CO value	√			√	
FTND scores	√	√	√	√	
MNWS	√	√	√	√	
QSU-Brief scores	√	√	√	√	

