### Statistical analysis

The SPSS 26.0 software will be used for analysis. Measurement data will be expressed as *mean ± SD*, and enumeration data will be expressed as rate. Repeated measurement analysis of variance will be used for intra-group comparison of measurement data satisfying normal distribution, and SNK (Student-Newman-Keuls) method will be used for inter-group comparison; quantitative data will be tested by *χ*^*2*^. Nonparametric tests will be used for data that do not meet the normal distribution and equal variances. *P* ≤ 0.05 will be considered significant. PPS (per-protocol set) will be used in the current study, and only the data will be analyzed from the participants who will perform the whole process. For those who lack follow-up data, the data of the last observation carried forward.

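### Relapse rate, a main outcome, compares week-8 quitters only (about 2 of 24 expected on double placebo), and the two rules for lost participants conflict, one of them lowering recorded relapse

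*Protocol article*

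**What the plan says.** Under Primary outcome: "Abstinence rate, relapse rate, and expiratory CO value will be selected as the main outcome indexes". On how the first two are assessed: "The former two are mainly judged by the self-report of the participants at the end of treatment and follow-up". Table 3 has abstinence assessed at week 8 and at the end of follow-up, and relapse once, at the end of follow-up. No denominator for relapse is printed.

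The Sample size calculation section gives the planning rates: "The withdrawal rates of acupuncture (*p*_1_) and placebo (*p*_2_) will be 56% [18] and 9.1% [19], respectively". It allows for 30% loss and arrives at 24 per group, 96 in total.

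The Statistical analysis section gives two rules for people who are lost. One is a per-protocol set limited to participants who complete the whole process. The other follows directly: "For those who lack follow-up data, the data of the last observation carried forward".

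The Introduction closes with the hope that the trial will "provide effective smoking cessation methods with lower relapse rates for smokers".

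**The concern.** Only a person who has quit can relapse. With the Table 3 schedule, the people at risk are those abstinent at week 8, and that group is produced by the treatments being compared. An arm that helps more marginal quitters could show a higher relapse rate while leaving more people smoke-free. Randomisation does not protect this comparison, and in the sham/sham arm it may have almost no one in it.

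The handling of loss adds a second problem. For a week-8 quitter who disappears during follow-up, the last abstinence record is abstinent. Carrying it forward records no relapse, whatever happened. Excluding the person instead gives a different relapse rate from the same data. The plan prescribes both, for an outcome it ranks among its main ones.

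**Working it through.** **Inputs.** From Sample size calculation: p1 = 0.56, p2 = 0.091, α = 0.05, power 90%, 18 per group before loss, 30% loss, 24 per group. The text calls p1 and p2 withdrawal rates. I read them as quit rates, because only that fits an efficacy calculation and loss has its own 30%. I apply 0.091 to the sham/sham arm and 0.56 to acupuncture with sham patch. No quit rate is given for either active-patch arm, and no relapse rate for any arm.

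**Reproducing the plan's figure.** In the printed formula with two-sided α, p = (0.56 + 0.091)/2 = 0.3255 and

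N = [1.96 × √(2 × 0.3255 × 0.6745) + 1.2816 × √(0.2464 + 0.0827)]² / 0.469² = 18.8.

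This rounds up to 19, one above the stated 18; one-sided α gives 15.1, so 16. The 24 follows from 18 × 1.3 = 23.4. The inputs are therefore read as intended.

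**Expected week-8 quitters.**

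| n per arm | Acupuncture (n × 0.56) | Sham/sham (n × 0.091) | P(no sham/sham quitter) | P(at most one) |
|---|---|---|---|---|
| 24 | 13.4 | 2.2 | 0.909²⁴ = 10% | 34% |
| 17 (24 × 0.7 = 16.8) | 9.5 | 1.5 | 20% | 53% |

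The second row applies if 30% of each arm is excluded as non-completers.

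**What such counts can show.** An observed 1 of 2 relapsing has an exact 95% interval of 1% to 99%. With 13 v 2 quitters, Fisher's exact test reaches P ≤ 0.05 in favour of acupuncture only if both sham/sham quitters relapse and at most 1 of 13 acupuncture quitters does (p = 0.029; 2 of 13 gives 0.057). With 10 v 1 quitters the smallest attainable p is 0.09. Letting the number of quitters vary, with 24 per arm and no loss, power is about 5% for true relapse of 30% v 60% and about 24% for 20% v 80%. These relapse rates are assumptions.

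**Effect of carrying the last observation forward.** Let r be the relapse rate among quitters who are seen and l the share of quitters lost. Every lost quitter is recorded as not relapsed, so recorded relapse = r × (1 − l).

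| r | l = 15% | l = 30% |
|---|---|---|
| 30% | 25.5% | 21% |
| 50% | 42.5% | 35% |
| 70% | 59.5% | 49% |

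If the lost relapse at the same rate as the seen, the true figure is r. If all of them relapse, the truth at r = 50% and l = 30% is 0.35 + 0.30 = 65%, still recorded as 35%. A lost quitter who stayed abstinent is recorded correctly, so among quitters the error runs one way only.

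**Unequal loss.** With true relapse of 50% in both arms, the same in the lost and the seen, and loss of 10% v 40%: 0.5 × 0.9 = 45% v 0.5 × 0.6 = 30%. A 15-point difference appears where there is none.

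**The two rules side by side.** If completing the whole process means all 16 weeks, a quitter lost in follow-up is excluded and there is essentially nothing to carry forward for these outcomes. If it means the 8-week treatment course, that quitter stays in and is carried forward as abstinent. With r = 50% and l = 30%, the first reading reports 50% on a smaller denominator; the second reports 35%.

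**The case against.** **The completers-only sentence.** A reader might infer that every lost quitter will be recorded as not relapsed. The text does not establish that: read strictly, the per-protocol sentence removes such people. This objection stands. The supportable point is that the two rules conflict, that one of them biases relapse downwards, and that the other shrinks an already small group and is unbiased only if loss is unrelated to relapse.

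**The denominator is inferred.** The article prints none, and a condensed article may leave it to a fuller document. That is fair. Still, no other denominator fits the meaning of relapse and the Table 3 schedule, except counting relapse over everyone randomised, where an arm with few quitters would look good for the wrong reason.

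**Sparseness is shown for one arm only.** A reader might conclude that the trial can say nothing about relapse. The figures do not go that far. About 13 quitters are expected on acupuncture, and the active-patch arms have no planning rate. Comparisons among the active arms may be less sparse, though still not randomised.

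**Abstinence at the end of follow-up is already a main outcome.** Observed relapse therefore already counts as failure there. This is true and limits the damage, but that outcome falls under the same two conflicting rules.

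**How much weight relapse carries.** The remark on lower relapse is in the Introduction; the Objectives section speaks only of effect and safety. The case rests on relapse being a main outcome, not on that remark.

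**Conclusion.** The point holds in limited form. Relapse rate among week-8 quitters is not a randomised comparison between any arms. Against sham/sham it is very sparse: about 2 expected quitters of 24, a 10% chance of none and 34% of at most one. The Statistical analysis section gives two incompatible rules for lost participants. Where the last observation is carried forward, recorded relapse is 0.70 times the rate among those seen at 30% loss, and 10% v 40% loss creates a spurious 45% v 30%.

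This rests on three assumptions: the planning figures are quit rates, relapse is counted among week-8 quitters, and the overall 30% loss applies to quitters. The direction of the bias needs only the second.

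A reader might go further and say that acupuncture abstinence would be reported as 56% when it is really 39% (0.56 × 0.7). That requires no observed quitter to relapse and every lost one to do so, and the documents support neither. Nor do they say that loss usually means relapse. The argument needs only that carrying forward cannot record a relapse in anyone lost.

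**What to change.** In Statistical analysis, for abstinence and relapse only, replace both the completers-only set and the carry-forward rule with analysis of all randomised participants in their assigned groups, counting missing abstinence as smoking. Keep the per-protocol analysis and alternative missing-data assumptions as sensitivity analyses. These are needed because counting missing as smoking is itself an assumption: in the unequal-loss example it would record failure among quitters as 0.45 + 0.10 = 55% v 0.30 + 0.40 = 70%.

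Draw the between-arm conclusion on lasting cessation from sustained abstinence, defined as abstinent at week 8 and at the end of follow-up, over all randomised. A relapse then counts as failure in a denominator fixed by randomisation. Report relapse among week-8 quitters descriptively as n/N per arm.

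**Cost.** Table 3 already collects both abstinence time points, so no new data are needed. Follow-up abstinence will look lower. For illustration, with 56% quitting, 50% relapse and 30% of quitters lost, carrying forward gives 0.56 × 0.65 = 36.4% and missing as smoking gives 0.56 × 0.7 × 0.5 = 19.6%, while the truth is 28% if the lost relapse like the seen. The trial is registered and Trial status describes recruitment as ongoing, so the change to a main outcome must be documented as an amendment, with its reason, before unblinding.

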### Eligibility criteria of the participants

#### Diagnostic criteria

According to the Diagnostic and Statistical Manual of Mental Disorders (DSM-IV) prepared by the American Psychiatric Association, Diagnostic Criteria for Nicotine Dependence 292.0:Daily use of nicotine for at least 3 weeksMore than 4 of the symptoms that occur within 24 h after stopping or reducing smoking: dysthymia or depression, insomnia, irritability, anger, anxiety, difficulty concentrating, restlessness, slow heart rate, and increased appetite or weight gainClinically significant distress due to the above symptoms or functional deficits in social, occupational, and other important aspectsThese symptoms are not due to a physical condition and cannot be attributed to any other mental disorder

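### Consecutive sentences give incompatible rules for participants with missing visits: completers only, and last observation carried forward

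*Protocol article*

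**What the plan says.** The protocol article's Statistical analysis section names one analysis set, the per-protocol set, and defines it by completion: "only the data will be analyzed from the participants who will perform the whole process". The next sentence reads: "For those who lack follow-up data, the data of the last observation carried forward". No other analysis set is named, and nothing limits carry-forward to particular outcomes, visits or participants.

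For the three scales (FTND, MNWS, QSU-Brief), the Secondary outcome section says: "Each patient will be asked a questionnaire prior to the treatment and at 1, 4, and 8 weeks after the treatment". Table 3 places weeks 1, 4 and 8 in the treatment period and ticks no scale at the end of follow-up. Expiratory CO, one of the three main outcomes, is ticked only before treatment and at week 8. The Sample size calculation section allows for substantial loss: "Considering 30% loss to follow-up rate, the sample size per group will be 24 cases".

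**The concern.** The two sentences cannot both be applied to the same person. Someone who performed the whole process has little to carry forward, and someone with data to carry forward did not perform the whole process. The analyst must choose, and the choice decides how many participants are analysed and whose values count.

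Neither rule suits outcomes measured at several visits. Completers-only analysis departs from the randomised comparison and discards real week-1 and week-4 scores. Carry-forward, where it reaches these outcomes, presents an early score as the week-8 score and treats it in the analysis of variance as a real observation. For CO it can only enter a pre-treatment reading as the outcome, because Table 3 has no visit in between.

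**Working it through.** **1. The plan's own figures.** Inputs from the Sample size calculation section: rates that "will be 56% [18] and 9.1% [19], respectively", alpha 0.05, power 90%. Sidedness is not stated; I assume two-sided. With p = (0.56 + 0.091)/2 = 0.3255:

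N = [1.960 × √0.4391 + 1.282 × √0.3291]² / 0.469² = (1.299 + 0.735)² / 0.2200 = 18.8, so 19.

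The plan states at least 18, which is close enough here. The 24 follows from 18 × 1.3 = 23.4, rounded up.

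**2. Number analysed under each sentence at 30% loss.**
- Completers only: 24 × 0.7 = 16.8 per group, 96 × 0.7 = 67 in total. For the comparison on which the trial was sized, two-sided power is 84.3% at 16 and 86.6% at 17 per group, against 90% planned.
- Carry-forward: 24 per group, 96 in total, with up to 24 × 0.3 = 7.2 per group contributing carried values.

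**3. What happens to a participant, by last visit attended.**

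| Last data at | Completers' rule | Carry-forward, if it covers treatment visits |
|---|---|---|
| Baseline | Excluded | Baseline score entered at weeks 1, 4 and 8; baseline CO entered at week 8 |
| Week 1 | Excluded, week-1 score discarded | Week-1 score entered at weeks 4 and 8; baseline CO entered at week 8 |
| Week 4 | Excluded, weeks 1 and 4 discarded | Week-4 score entered at week 8; baseline CO entered at week 8 |
| Week 8 | Excluded, if the whole process includes follow-up | Scales and CO unaffected; only abstinence has an earlier value to carry |

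**4. Effect of carry-forward on the week-8 arm contrast.** Let d be the share lost in an arm and D the fall in mean score from the last observed visit to week 8. If loss is unrelated to the score, an arm's week-8 mean is too high by d × D. With no true difference and the same D in both arms, the false difference is (d_B − d_A) × D. The documents give neither D nor loss by arm, so both are assumptions. With 24 per arm, D in SD units, unit variance and mixture variance 1 + d(1 − d)D²:

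| Loss | D = 0.5 | D = 1.0 | D = 1.5 |
|---|---|---|---|
| 30% / 30% | 0; 5% | 0; 5% | 0; 5% |
| 20% / 40% | 0.10 SD; 6% | 0.20 SD; 10% | 0.30 SD; 14% |

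(False difference; rejection rate of a nominal two-sided 5% test.) Example for D = 1.0: SE = √((1.16 + 1.24)/24) = 0.316; 0.20/0.316 = 0.632; 1 − Φ(1.960 − 0.632) + Φ(−1.960 − 0.632) = 0.097. With equal loss the arm difference is zero, but both week-8 means are still too high, by 0.15, 0.30 or 0.45 SD.

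**5. Simulation.** Assumptions: 24 per arm, SD 7, correlation 0.5, identical courses in both arms, week-8 mean 8, loss more likely at higher week-1 scores. Results for 20% against 40% loss:
- All loss straight after week 1, mean falling from 14 or 16: false-positive rate about 8% to 11%.
- Later loss, or a smaller fall: about 6.5% to 7.5%. Runs with a fall from 11.5 to 8 gave 5.4% to 6.7%, close to nominal.

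With 30% loss in both arms the rate is about 5%.

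**6. The alternative is not immune.** Observed week-8 data adjusted for the week-1 score showed no bias when loss depended only on that score, but that is the condition under which such an analysis is valid. When loss was made to depend on the unseen week-8 score, the observed-data analysis was off by roughly −0.7 to −1.3 points, over 20%/40% and 15%/45% loss. Carry-forward was off by about +0.7 to +1.1 points.

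**The case against.** The strongest reply is that carry-forward was never meant for the scales or CO. The Abstract describes 8 weeks of treatment and then 8 weeks of follow-up, the Primary outcome section separates the end of treatment from follow-up, and Table 3 has a distinct column for the end of follow-up with no scale or CO tick. On that usage the rule touches only abstinence. This is a fair reading and probably the commoner usage in the document. It is not written as a restriction, however. The Participant's management system section uses the term more loosely, and the Secondary outcome sentence describes the scale visits as coming after the treatment. Even on the narrow reading, the completers' sentence conflicts with carrying forward a missed end-of-follow-up value, and missing scale visits are still handled by exclusion alone.

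A second reply is that the two harms exclude each other: if the completers' sentence governs, no week-1 score ever becomes a week-8 score. That is correct, and it is why the point is the choice between two rules, each poor in its own way.

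A reader might go further and infer that the plan will produce false arm differences on the withdrawal and craving scales. The documents do not support that. They give only one overall loss figure and no score trajectories. The Diagnostic criteria section refers to "symptoms that occur within 24 h after stopping or reducing smoking", which describes onset and says nothing about the course to week 8. A reader might also infer that a mixed model removes the bias or needs a strictly weaker assumption than carry-forward. Neither holds: the assumptions differ, and neither implies the other.

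**Conclusion.** The contradiction is certain and rests on the text alone: about 17 or 24 per group are analysed at the planned 30% loss, depending on the sentence followed. It is also certain that completers-only analysis discards randomised participants and observed scores, and that any carry-forward of CO to week 8 enters a pre-treatment value.

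The false-positive figures are illustrations. About 6.5% to 11% applies under the assumed 20% against 40% loss, SD 7 and correlation 0.5, with the upper end reached only when all loss follows week 1 and scores fall by 6 to 8 points. With equal loss the rate stays near 5%. These figures show that the rule can matter; they do not predict what it will do in this trial. The plan should be changed before the data are analysed, because of the conflict and the poor fit of both rules to repeated measures.

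**What to change.** Replace both sentences as they apply to the scales and CO:

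- Make all randomised participants the main analysis set, with the per-protocol set as a sensitivity analysis.
- Delete carry-forward for MNWS, QSU-Brief and FTND. Analyse each with a mixed model for repeated measures on all observed visits (arm, visit, arm-by-visit, baseline score), and report the week-8 arm contrasts.
- Analyse week-8 CO with baseline CO as covariate. Report it both on observed values and with missing values set to baseline, because loss may be related to resumed smoking.
- Check the model's missing-data assumption with a sensitivity analysis.

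If carry-forward is meant to remain for abstinence at the end of follow-up, the text should say so and reconcile it with the analysis set.

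The cost is a change of wording and slightly more analysis work; the named SPSS 26.0 has a MIXED procedure. The downside is that the model assumes loss is explained by the scores already observed, an assumption different from carry-forward's that the data cannot confirm.

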### Participant’s management system

The informed consent will be obtained to all of the participants prior to the conduct of the study. The testers will be followed up regularly and given verbal spiritual encouragement to minimize dropout.

### Ancillary and post-trial care

At the end of the trial, we will provide free nicotine patch to the participants who have not achieved the cessation goal or effect until the desired effect is achieved.

## Discussion

Smoking is not only a physical dependence, but also a psychological dependence, thus, smoking cessation requires more than a strong will [21]. This study can only be carried out when the participants have certain intentions to quit smoking. We will choose two methods of NRT and acupuncture for the combined intervention of smokers who are willing to quit. Acupuncture is a relatively common and effective method in traditional Chinese medicine, while NRT is the most commonly used of the internationally recognized interventions. This combination is rarely reported in the literature, and it is expected to achieve better outcomes. We know that smoking behavior falls under the category of “mental and behavioral disorders resulting from the use of psychoactive substances” [22]. Thus, the choice of control group will not be a single intervention, but a combination of a placebo treatment of another method, as well as a group of pure placebo group. Each group will receive two interventions designed to blind the participants and provide a psychological cue that will help improve the effect of the intervention and promote participant compliance with the regulations.

There is a paradigm shift towards patient-centered care and active involvement of participants and public in research design and active participation throughout the research process [23]. However, to ensure the implementation of blind method in the later stage of the experiment, this paradigm has not adopted in the design of this study, and the protocol designers will be all composed of trial researchers, without the participation of the public or participants.

There are several limitations in the current study. First, although we chose the double dummy to try to blind the study participants, we are unable to blind the physicians, which may lead to some bias. However, all the subjective indicators are collected through the network background, which will minimize these biases to some extent. Secondly, although we have performed the sample size calculation, the sample size is still small, and a large sample test will be needed in the future stage.

Our study will evaluate the efficacy and safety of different interventions for smoking cessation, providing some evidence for smokers to choose smoking cessation programs, as well as for future studies, and promote the development of acupuncture for smoking cessation. The results will be published within 6 months after the trial completed.

